## 4.3. Statistical methods

### 4.3.1. Overview

All statistical analysis will be conducted on an intention-to-treat basis, i.e. all randomized participants with baseline and at least one post-baseline measurement will be analyzed by original treatment assignment, regardless of adherence. Baseline characteristics will be described and compared between groups using summary measures (e.g. means, medians, rates) and tests selected based on variable distribution. Analyses will be adjusted for factors used in the stratified randomization (center, age group and type of cancer). In addition, if, despite efforts to standardize intervention delivery (section 5.1), we identify substantial differences in fidelity across sites, we will evaluate effect modification by site including the site  $\times$  intervention interaction in the models. The False Discovery Rate criterion will be used to correct for multiple testing in non-planned analyses. Co-I [name] has been the primary biostatistician for all prior PQ analyses and is best suited to head the PQ Response's analysis, along with her team at Deakin University. The PI and Co-I [name] will be part of the leadership team. While all Co-Is will be involved in analysis and manuscript writing, some may take a more prominent role according to their specific expertise (e.g. [name], [name] with aim 2, and [name] with aim 3). DFCI will coordinate data cleaning and programming.

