## 2.3. Interventions

### 2.3.1. Description of Interventions

Following consent and run-in period, responders will be randomized (1:1) to PediQUEST Response (intervention) or usual cancer care (control) arms (week 0). The PI and Project Manager may together, rarely, decide to randomize a dyad that does not strictly meet the “responder” criteria, if, for example, there were technical or other issues that reasonably prevented them from becoming responders. Participants without home internet (<10%) will be provided a tablet with cellular service during the study.

If participation in the run-in period needs to be paused for any reason, resulting in delayed randomization, participants will be notified and allowed to continue or restart on the study with PI approval.

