Participants' adherence to study procedures will be facilitated by a relatively short follow-up, flexibility in scheduling interviews, and working with experienced RCs (in at least two of the sites the RCs have already worked in prior or related projects of this group). Adherence with the PQ system will be enhanced in both arms through the automated emails/notifications sent to participants reminding them to fill in their assigned surveys. In addition, when a participant/family does not answer a PQ-Survey or declines to meet with Response team, RCs will contact the family over their preferred route of contact (phone or email) to discuss any difficulties and their willingness to continue participation. As a token of appreciation, the patient and one parent will each receive a \$40 Amazon gift card for every 4 weeks of study participation. \$20 dollars will be provided to patient and one parent for participating in the two-week run-in period.

Participants' adherence will be monitored by the PM during study meetings (recurrence of these meetings will be flexible, with at least a monthly meeting). If either parent or child misses four consecutive PediQUEST surveys, the dyad will be removed from the study. Rare exceptions to this criterion may be granted at the discretion of the PI and PM.

| Process                                     | Indicators                                                                                                                                                                                                                    | Source                     | Period  | Target |
|---------------------------------------------|-------------------------------------------------------------------------------------------------------------------------------------------------------------------------------------------------------------------------------|----------------------------|---------|--------|
| Intervention component                      | 1. No. Times Visit Occurs within 3 wks randomization/ No. randomized to intervention                                                                                                                                   | MR*                        | Monthly | >90%   |

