## 2.4. Outcomes

### 2.4.1. Primary Outcome Measures (aim 1)

Child Quality of Life: Difference between the two treatment arms in the mean over 16-weeks (16-w) of PedsQL total score as reported by (a) the parent for all enrolled patients, and (b) the patient if 5 years of age or older. PedsQL scores range from 0-100 (higher better) and are calculated as the average of all 22 items (total score). For each weekly administration, scores are calculated if >50% of the PedsQL items are answered. Treatment success will be defined as a difference of at least the minimal clinically important difference (MCID) between groups. The MCID for PedsQL total score is 4.4 points.

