### 3. Methods: Assignment of interventions

#### 3.1. Allocation (sequence generation, concealment, and implementation)

Participants will be randomly assigned to the intervention or control group with a 1:1 allocation as per a computer-generated randomization sequence created by study statistician, co-I [name], and stratified by center, age (2-7, 8-12,  $\geq 13$  years old), and type of cancer (hematological, non-hematological malignancies). Study personnel will not have access to the sequences. Random sequences will be embedded in REDCap by informatics personnel, ensuring best practice standards for allocation concealment. Two weeks after enrolling, at week 0, if participant meets the criteria of being a responder, i.e. having answered two or more PQ-surveys, regardless of who in the dyad answered them, the RC will be able to see study arm assignment in REDCap. The RC will begin intervention procedures by turning on the PQ-feedback report and email features of PQ web,

notifying the primary team and linking the account to the corresponding providers (primary oncologist, primary nurse, primary psychosocial clinician, and PC Response team key person) so they start to receive reports too, and letting the PC Response team administrative designated person know of the assignment so they can schedule the initial visit with the Response team (as explained in 2.3.1 and Figure 7).

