### 3.2. Blinding

After randomization, participants, PC team, oncologists, and research staff will be unblinded to group assignment, because the intervention is not amenable for blinding.

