### 4.3.2. Analysis Plan

#### 4.3.2.1. Comparison of patient-level outcomes (HRQoL and Symptom distress) - Specific Aim 1

The effect of the intervention on child quality of life and symptom burden outcomes (see section 2.4) will be estimated using mixed linear models, with patient as a random effect and group, time (categorical) and group x time interaction and the stratification factors as fixed effects. . The same analysis will be undertaken for the respective domain subscales of PedsQL (physical and psychosocial) and PQ-MSAS (physical and psychological).

#### 4.3.2.2. Comparison of parent-level outcomes (anxiety, depression, HRQoL, and burden) - Specific Aim 2

The same analytical approach described for patient-level outcomes will be followed to analyze parent S-TAI-State, CES-D-10 mean scores and aRSQ symptom-related scores. In S-TAI-State analysis, we will additionally adjust by baseline S-TAI-Trait score. We will also compare depression (CES-D-10  $\geq 10$ ) over time between the two groups using generalized linear mixed models with logit link and binomial distribution. As gender is a predictor of these outcomes, it will be included in these models if imbalanced between arms.

#### 4.3.2.3. Comparison of family activation outcomes - Specific Aim 3

Mixed models, similar to those described for patient-level outcomes, will be fitted to estimate the effect of the intervention on change between week 16 and baseline in Brief COPE active coping, planning, and instrumental support Scores, Total No. of, and No. of different, complementary therapies, and No. of psychosocial clinician encounters over the 16-w study period. Link and distribution for these models will be defined based on the distribution of the outcome variable. We will explore whether change in parent's activation score is modified by parent/child characteristics (e.g. parent's gender, S-TAI-Trait, CES-D-10 scores; and child's diagnosis, among others) including the corresponding interaction terms.

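### Section 4.3.1 makes a baseline score a condition of the intention-to-treat set, although the primary endpoint and model do not need one; usable follow-up scores would be discarded, with a small expected loss

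*Protocol*

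**What the plan says.** **Analysis set.** Section 4.3.1 states: "All statistical analysis will be conducted on an intention-to-treat basis". The same sentence then defines the set as "all randomized participants with baseline and at least one post-baseline measurement will be analyzed by original treatment assignment, regardless of adherence". No other section defines a set of all randomised participants.

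**Primary endpoint.** Section 2.4.1: "Difference between the two treatment arms in the mean over 16-weeks (16-w) of PedsQL total score as reported by" parent and patient. This is a level after randomisation, not a change from baseline. Section 1.3.2 says that the two informants are analysed separately.

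**Primary model.** Section 4.3.2.1 specifies a linear mixed model "with patient as a random effect and group, time (categorical) and group x time interaction and the stratification factors as fixed effects". The baseline PedsQL score is not among the terms.

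**Who can be randomised.** Section 3.1 defines a responder as "having answered two or more PQ-surveys, regardless of who in the dyad answered them". Section 1.3 asks for two surveys per participant, and section 1.3.1 requires both patient and parent to be responders. Section 2.3.1 lets the principal investigator and the Project Manager, on rare occasions, "decide to randomize a dyad that does not strictly meet the" responder criteria.

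**Parent distress scores.** In Table 3 (section 2.5.1) the S-TAI-State and CES-D-10 are first given at week 0. The run-in rule counts only PediQUEST surveys, so it does not secure a week-0 value on either scale.

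**The concern.** Two conditions are attached to the label. Each could matter, but in different ways.

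The baseline condition can remove people who have outcome data. A child with weekly self-reports after randomisation but none from the run-in would be left out of the patient-report primary analysis, although the model could use every one of those reports. A parent who skips the week-0 questionnaire and answers at weeks 4 to 16 would be lost from the anxiety and depression analyses in the same way. Randomised participants would be excluded, and data wasted, with nothing gained.

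The post-baseline condition depends on what happens after an open allocation; section 3.2 says that "participants, PC team, oncologists, and research staff will be unblinded to group assignment". Whether a family returns any score may therefore depend on arm. At stake here are the accuracy of the label, the reporting of exclusions by arm, and which participants the missing-data analyses in section 4.3.3 may cover.

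**Working it through.** **1. Does the primary analysis need a baseline score?** The endpoint in section 2.4.1 uses scores over the 16 weeks. The model in section 4.3.2.1 has group, time, their interaction, the stratification factors and a patient effect. If week 0 were taken as one level of categorical time, a likelihood-based mixed model would still use a participant whose week-0 value is missing. The condition is not needed under either reading. For S-TAI-State, section 4.3.2.2 adds the baseline S-TAI-Trait score as a covariate. That is a different instrument from the Baseline Packet, so the week-0 State score itself is still not required.

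**2. Can someone have follow-up scores but no baseline?** I apply the condition to each informant, since informants are analysed separately.

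- Section 3.1: two parent surveys suffice, so a child may have none.
- Sections 1.3 and 1.3.1: each informant must have answered at least two surveys (1.3.1 counts these out of three), so this should not happen.
- Section 2.3.1: the exception can admit such a child under either rule, but it is meant to be rare, and missing the two-survey threshold does not mean having no score.
- Table 3: a parent may miss week 0 on S-TAI-State or CES-D-10 under any version of the run-in rule.

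The protocol also does not say which run-in survey is the PedsQL baseline, so membership of the set is not fully fixed.

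**3. The plan's own power figure.** Inputs from section 2.6.1: difference δ = 4.4, SD σ = 9.5, one-sided α = 0.05, n = 68 per arm.

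Power = Φ(δ / (σ√(2/n)) − 1.645). With n = 68, 4.4 / (9.5 × √(2/68)) = 2.701, and Φ(2.701 − 1.645) = 85.4%. The stated 85% is reproduced (85.1% with the noncentral t). The sample-size chain in section 2.6 also holds: 200 × 0.75 = 150 randomised, and 150 × 0.90 = 135 against the stated 136.

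**4. Loss from the baseline condition.** The share without a baseline is not in the protocol, so a range is assumed. Same formula, starting from 75 per arm:

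| Share excluded (assumed) | Participants of 150 | Power |
|---|---|---|
| 0% | 0 | 88.3% |
| 2% | 3 | 87.8% |
| 5% | 7.5 | 86.9% |
| 10% | 15 | 85.2% |

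For 0 to 5%, the loss is 0 to about 1.5 points. The patient-report analysis is smaller because it starts at age 5. If it has 115 children (assumed) and 5 lack a baseline (5/115 = 4.3%), power goes from 79.9% to 78.3%, a loss of 1.6 points. The range is therefore about 0 to 2 points. The 10% row is a pessimistic bound: the protocol's 10% attrition is loss during follow-up, not a missing baseline.

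**5. Effect of the post-baseline condition on the primary estimate.** A participant with no post-randomisation score supplies no post-randomisation outcome to the mixed model. Naming that participant as in or out of the set leaves the primary estimate the same.

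**The case against.** The definition is open. The sentence that uses the intention-to-treat label also states both conditions, and participants are analysed as assigned whatever their adherence. Sections 1.3 and 1.3.1 make a missing PedsQL baseline unlikely. Section 4.3.3 already plans multiple imputation or inverse probability weighting, sensitivity analyses for data not missing at random, and a check of robustness. Counts by arm are commonly left to a statistical analysis plan, which is not shown here.

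Most of this stands, and it keeps the point small. It does not rescue the baseline condition, which the protocol fixes explicitly and which has no use in the planned primary model. Section 4.3.3 does not say that it brings excluded participants back, so the set as written limits who enters those analyses.

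A reader might infer more: that the rule biases the primary result. For example, an assumed 3-percentage-point difference between arms in families who stop at once, times an assumed 8-point lower score in those families, gives 0.03 × 8 = 0.24 points. That figure should not be charged to the rule. It describes missing outcomes, and redefining the set would not remove it, as step 5 shows. A reader might also infer from section 3.1 alone that many children will lack a baseline. Sections 1.3 and 1.3.1 say otherwise, and the conflict between them has to be settled first.

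**Conclusion.** The point holds in a limited form. The set in section 4.3.1 is a modified intention-to-treat set, and its baseline condition would discard usable post-randomisation scores without serving the primary endpoint or model. The routes to such a loss are the wording of section 3.1, the exception in section 2.3.1 and, for parent distress, a missed week-0 questionnaire.

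For the primary outcome the expected cost is about 0 to 2 points of power. This rests on the assumption that 0 to 5% of participants are affected and, for self-report, on an assumed 115 children. The loss for parent distress cannot be sized from the protocol. No stated figure is wrong on this point. The documents support neither a claim of bias in the primary estimate from the post-baseline condition nor a claim that the definition is hidden. That condition matters for the label, for reporting by arm and for the scope of the missing-data analyses.

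**What to change.** In section 4.3.1, define the primary set as all randomised participants by assigned arm, delete the baseline requirement, and state that every post-randomisation score enters the mixed model. If a baseline covariate is added later, say how a missing value is handled, for example by the overall mean or by modelling baseline as part of the outcome vector.

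State that participants with no post-randomisation score will be counted by arm and included in the sensitivity analyses of section 4.3.3. This improves reporting and leaves the primary mixed-model estimate unchanged.

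Reconcile the responder rule in section 3.1 with sections 1.3 and 1.3.1.

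The cost is two or three sentences in section 4.3.1 and one consistent responder definition. No new data are needed.

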## 1.3. Trial Design

We will conduct a randomized, controlled, un-blinded, multisite, effectiveness trial with two parallel groups, PQ Response (intervention) vs. usual cancer care (comparator or control). Primary outcomes will be the mean over 16-weeks of the child HRQoL total score reported by (a) the parent and (b) the patient if ≥5 years of age. Randomization will be stratified by site, age, and type of cancer with a 1:1 allocation. We intend to enroll a total of 200 expecting to achieve our target sample size of 136 pediatric oncology patients ≥2 years old with advanced cancer (N=68/arm) from five participating sites over a 36-month period (start times staggered by site, see more in section 2.6 Sample size). The expected start for enrollment is September 2017.

Families (patient and one of the parents) will be enrolled for a total of 18 weeks. After an initial 2-week run-in period, families who answered a total of at least two PediQUEST surveys per participant during the run-in period (responders), will be randomized to the intervention or usual care (Figure 4).

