### 1.3.2. Rationale for using parent and patient reports to measure patient outcomes

The primary study goal is to evaluate the effects of PQ Response on patient HRQoL and symptom burden across a wide age range of children, adolescents, and young adults (AYA). While self-report remains the gold-standard for these type of outcomes, there is an increasing body of evidence suggesting that in the case of children/AYA there is considerable value in having both parent and child/AYA reports. Each informant in the parent-patient dyad provides a unique perspective, influenced by their experience, personal characteristics, role, and environmental aspects, among others. Together, these reports provide a broader picture of the child/AYA's situation. Yet, one of the consequences of using "multiple informants," is that the information may be non-concordant (divergent). The optimal approach to consolidate multiple informant responses into a unique child/AYA outcome is still unresolved. Acknowledging the clinical importance of considering both "voices" (i.e. patient and parent), we will measure patient outcomes (HRQoL and symptom burden) using both parent and patient reports. The chosen instruments allow parental report across the study's full age range, and patient self-report from the age of five for HRQoL, and from the age of 7 for symptom burden (however, because the younger child version of the symptom instrument for ages 7-12 does not measure the full range of symptoms we will not use it as an outcome measure, see section 2.4.2.1 for details). Given the lack of consensus as to how to handle multiple informant information, the effects of the intervention on patient outcomes will be analyzed separately for each of these informants. Of note, the data collected in this trial will also provide the opportunity to explore convergence and divergence of child/AYA and parent reports.

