| Scoring range                                                                                                                                                                                                                                                                                                                          | 0-100 (100=worse)                                                                                                                |       |       | 0-100 (100=better)                                                                                                                                      |     |      |     |             |      |     | 0-100 (100=better)                                                                                           |             |

\*The collection of both parent and child data will be used only to analyse concordance. PediQUEST reports only provide feedback on child answers (or parents when children are young or do not want to answer); † PQ-MSAS 7-12 evaluates shorter time frame (past two days) and only 8 symptoms; \*Response types: L-5: 5-option Likert type; L-4: 4-option Likert type; FS-3: 3-option Faces scale; VAS: Visual analogue scale (100 mm); §Data from PQ RCT

| Monthly Parent Questionnaires (weeks 0-4-8-12-16) |                        |                                                                                   |                                                                                                                                                                                                                                                                                                                                                                                                                                                                                                                                                               |

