### 2.6.1. Power considerations

Although the SS is mainly driven by pragmatic considerations (target population is small), power calculations were conducted and indicate that our projected minimal SS of 68 children per group provide sufficient power for both primary and secondary outcomes for clinically meaningful effect sizes. All power calculations presented below were computed with two sample independent one-side tests,  $\alpha=0.05$  unless otherwise specified. For Aims 1 and 2 power estimates are conservative because they only use one observation per subject (average across time) without accounting for the repeated measures within subject.

*Aim 1 HRQoL (primary) and Symptom (secondary) outcomes:* Standard deviations for these outcomes were estimated using data from our PQ study (39 weeks follow up, surveys answered when attending clinic or once a month). For each child, we identified all 16-w periods with  $\geq 6$  surveys and calculated mean PedsQL total and mean PQ-MSAS total scores for each 16-w period. We randomly selected one period per child and estimated the standard deviation of 16-week PedsQL means (SD). Strategy was repeated 10 times and a pooled estimate was calculated. A sample size of 136 children (68 per group) achieves 85% power to detect a 4.4 point increase (MCID) in the mean over 16-w PedsQL Total score (SD for both groups 9.5), and a 95% power to detect a 3-point decrease in mean over 16-w PQ-MSAS total score (SD = 5.3). These power calculations are conservative as they are based on mixed responses coming from parents and children, while in the current proposal responses from different informants will be considered in separate analyses and are expected to have less variability.

*Aim 2 Parental anxiety (S-TAI-State), and depression (CES-D-10) (secondary outcomes):* A sample size of 68 parents per group achieves more than 80% power to detect a moderate to large effect size (Cohen's  $d = 0.43$ ). For example, this effect size would correspond to a difference of 5.2 points in mean S-TAI-State (SD=12.2).

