### 5.1.3. Interim Analysis

A blinded primary end-point interim analysis will be conducted by LO at months 12 and 24 after the study opens. The DSMB will determine a priori stopping rules for efficacy and/or occurrence of serious events (the latter is described under Safety Monitoring, section 5.2.3). For efficacy endpoint, if the stopping rule is reached the DSMB will be presented with unblinded results (i.e. they will be able to ascertain which results correspond to the intervention arm). Based on these results, the DSMB will present recommendations to the Steering Committee regarding early stopping or continuation of the trial. Given the minimal risk involved, the modest benefit anticipated, and characteristics of the intervention, which make it unlikely for there to be a concurrent breakthrough result from another study, no changes in the course of this study are expected.

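### Two primary outcomes are analysed separately with no rule on whether one or both must succeed, and the only multiplicity correction is confined to non-planned analyses

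*Protocol*

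**What the plan says.** Section 1.3 sets two primary outcomes: "Primary outcomes will be the mean over 16-weeks of the child HRQoL total score reported by (a) the parent and (b) the patient", the latter from age 5. The WHO Summary, the Protocol Summary and section 2.4.1 agree. Section 1.3.2 acknowledges that the two informants may diverge and says that effects "will be analyzed separately for each of these informants".

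Section 2.4.1 defines treatment success as a between-group difference of at least the minimal clinically important difference (MCID), 4.4 points on the total score. Neither that section nor hypothesis H1 in section 1.2.1 says which informant must show it, or whether both must.

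The only significance level in the protocol is in section 2.6.1: "All power calculations presented below were computed with two sample independent one-side tests", with alpha 0.05. The calculation there is for a single comparison. On multiplicity, section 4.3.1 has one sentence: "The False Discovery Rate criterion will be used to correct for multiple testing in non-planned analyses". A footnote to Table 3 (section 2.5.1) says: "The collection of both parent and child data will be used only to analyse concordance".

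**The concern.** With two primary outcomes and no decision rule, the trial could be reported as positive on whichever informant came out favourably, and the rule could be chosen after the results are known. That matters here because the protocol itself expects the informants to disagree at times.

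This is more than detail left to a statistical analysis plan. By naming a correction and restricting it to non-planned analyses, the protocol places the planned primary tests outside it. An analysis plan that followed this text would leave them uncorrected, and one that corrected them would go beyond it. The decision rule is also part of defining the primary outcome. What is at stake is the error rate of the trial's main claim, which is currently undefined.

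**Working it through.** **Inputs.** From section 2.6.1: 68 per arm, difference 4.4, SD 9.5 in both groups, one-sided alpha 0.05, stated power 85%. From sections 1.3 and 2.4.1: two primary outcomes. The correlation between the two test statistics is not given, so a range is assumed.

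**Reproducing the stated power.**
- SE = 9.5 × √(2/68) = 1.63, so 4.4/1.63 = 2.70.
- One-sided 5%: power = Φ(2.70 − 1.645) = 85.4% (85.1% with the t distribution). The stated 85% is reproduced.
- Two-sided 5%: Φ(2.70 − 1.960) = 77.1% (t: 76.5%). This does not reproduce it, so the planning alpha is one-sided 5% for one test.

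**Chance of at least one false primary claim, if either informant suffices at one-sided 5% each.** Under independence it is 1 − 0.95² = 9.75%. With correlation ρ it is 1 − Φ₂(1.645, 1.645; ρ):

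| Assumed ρ | Familywise error |
|---|---|
| 0 | 9.75% |
| 0.3 | 9.3% |
| 0.5 | 8.8% |
| 0.7 | 8.0% |
| 0.8 | 7.5% |
| 0.9 | 6.8% |

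Both informants rate the same child, so positive correlation is expected and 9.75% is the ceiling for non-negative ρ.

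**If both must succeed.** A false claim of success on both needs every false null to be crossed, so the error is at most 5%. There is no inflation.

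**Power at 68 per arm when only one outcome responds.**
- Family at one-sided 5%, hence 2.5% for the smaller p-value: Φ(2.70 − 1.960) = 77.1% (t: 76.5%). Keeping 85% would need 84 per arm.
- Family at two-sided 5%, hence two-sided 2.5%: Φ(2.70 − 2.241) = 67.7% (t: 66.8%). Keeping 85% would need 101 per arm.

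**Patient report.** Section 2.5 has only parents answering for ages 2 to 4, so this test has fewer than 68 per arm. The share is not given. Same SD, illustrative numbers per arm:

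| Assumed n per arm | Power, one-sided 5% | Power, one-sided 2.5% |
|---|---|---|
| 61 | 81.9% | 72.5% |
| 54 | 77.7% | 67.2% |
| 48 | 73.4% | 62.1% |

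**The case against.** The strongest objection is that the success rule in 2.4.1 may already be strict. If it means that the observed difference must reach 4.4 points, then under the null this is z = 2.70, a chance of about 0.35% per outcome and at most 0.7% for either at 68 per arm. That would remove the concern about false claims. But the section does not say whether the observed or the true difference is meant. The observed reading also fits poorly with the power section: if the true difference were exactly 4.4, the estimate would fall short about half the time, against a stated power of 85%. So the rule needs explaining and cannot be relied on as error control.

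A second objection is that the outcome definitions join the two informants with *and*, which could mean that both are required. That is possible, but no section says so.

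Three stronger readings are tempting and are not supported:
- A reader might infer that the false-positive risk is nearly double a stated rate. The protocol states no familywise rate. One-sided 5% appears only in the power section, and the near doubling needs both independence and an either-informant rule.
- A reader might infer that the many planned secondary outcomes must also be corrected. They are labelled secondary, many overlap by construction (totals with their own subscales, two informants on one scale), and correcting them is a matter of preference.
- A reader might infer that the interim analyses at months 12 and 24 inflate the error further. Section 5.1.3 says "The DSMB will determine a priori stopping rules for efficacy". Nothing indicates an unadjusted boundary, and its form can properly sit in a charter or analysis plan.

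**Conclusion.** The point stands as a gap in the primary decision rule. The protocol has two separately analysed primary outcomes, no statement of whether one or both must succeed, and one correction whose scope excludes them. If either suffices at one-sided 5% each, the familywise error is up to 9.75%, and about 7.5% to 9.3% at assumed correlations of 0.8 to 0.3, which is roughly 1.5 to 1.9 times the planning alpha. These figures assume no further restriction from the MCID rule. If both must succeed there is no inflation, but the 85% then describes one test and not success on both. The documents do not allow that joint power to be computed.

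The Table 3 footnote is a plain contradiction of the dual primary outcome. Sections 1.3, 1.3.2 and 2.4.1 are consistent with one another, so it is a wording conflict to reconcile and does not call the design into doubt.

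**What to change.** Before anyone sees outcomes by arm:

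1. State in 2.4.1 and 4.3.1 whether one or both informants must succeed, and give the alpha and sidedness of the primary tests.
2. State how the 4.4-point rule relates to the test: a requirement on the observed difference, or a benchmark for interpretation.
3. If one informant suffices, test the two primary outcomes as one family at the planned overall alpha. Hochberg or Holm treats the informants equally: each allows both claims if both p-values meet their thresholds, and needs half of alpha for a lone success. Hochberg relies on non-negative dependence, which is reasonable here. A fixed sequence avoids splitting alpha but ranks the informants, and the second cannot be claimed if the first fails.
4. Reword the 4.3.1 sentence so that it no longer implies that planned primary tests go uncorrected.
5. Reconcile the Table 3 footnote with the primary outcome definition.
6. Restate power for each informant separately.

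The text changes are small, but the power cost under Hochberg or Holm should be disclosed: from 85% to about 76-77% when only one outcome responds, about 67% if the family is tested at two-sided 5%, and less for patient report. Restoring 85% by size alone would take 168 analysed dyads (84 per arm). At the protocol's own 25% non-response and 10% attrition, that is 168/(0.75 × 0.90) ≈ 249 enrolled against a target of 200. Requiring both informants, or a fixed sequence, needs no alpha split; requiring both lowers the chance of overall success.
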